### 1.9.3 Blinding

This is a single-blind (observer-blinded) trial. The primary and secondary outcomes will be obtained at baseline, in week 5 after 7 treatment sessions, in week 10 at the end of treatment and at follow-up (6 months after randomization) by the rater, who will be blinded to the treatment arm allocation. After the baseline visit, the participants will be randomized to either of the two treatment arms (1:1 randomization, see section 15.2.).

### 1.9.4 Time schedule

**Table 1:** Time schedule (estimated)

|                                      |                                |
|--------------------------------------|--------------------------------|
| Duration of trial:                   | 36 months                      |
| Recruitment period:                  | Q2/2018 – Q2/2020              |
| First patient first visit (FPFV):    | Q2/2018                        |
| Last patient last visit (LPLV):      | Q2/2020                        |
| Data base clearing/analysis:         | Q2/2020 – Q3/2020              |
| Trial report:                        | Q1/2021                        |
| Period of time for patient in trial: | 6 months                       |
| Screening period:                    | 1 week                         |
| Treatment period:                    | 8 weeks                        |
| Follow-up period:                    | 6 months (after randomization) |

### 1.9.5 End of trial

The end of trial is defined as the last visit of the last subject (subject number 248).

## 1.10 TRIAL POPULATION

### 1.10.1 Definitions

Subject definitions and subject completion:

- **Enrolled** subjects are those on whom trial specific investigations are performed after informed consent is given.
- **Randomized subjects / subjects assigned to treatment** are those allocated to one of the therapeutic interventions.
- **Treated** subjects are those who have completed at least 9 sessions in one of the therapeutic intervention as scheduled in the trial protocol.
- A **“completed”** subject is one who has completed all sessions of the therapeutic intervention and the follow-up session as scheduled in the trial protocol.

- A “**drop-out**” is an enrolled subject who stops prematurely before session 9 of the intervention. This can be due to non-observance of the protocol or to reasons unrelated to the trial, e.g., “moved away” or who are otherwise lost before final examination as scheduled. A subject who simply wishes to terminate the trial should also be considered as a drop-out.
- A “**withdrawal**” is an enrolled subject who stops prematurely or is withdrawn by the Investigator for reasons related to the trial, e.g., an adverse event.

## 1.10.2 Selection of trial population

### 1.10.2.1 Recruitment procedure

Subjects will be recruited consecutively if they suffer from late-life depression, fulfill the inclusion criteria, do not meet any exclusion criteria and have signed the informed consent.

Participating sites have been selected on the basis of being highly experienced in old age psychiatry, in the delivery of psychotherapy and in the running of clinical trials. All participating sites have outpatient clinics with several hundred patient contacts per year, including high numbers of patients with LLD. In addition, all sites collaborate with networks of psychiatrist and psychotherapist, which may be involved in patient identification. Further, advertisements will be placed at collaborating resident general and psychiatric practices.

### 1.10.2.2 Screening log

Each participating center will keep a log of all screened subjects with LLD.

### 1.10.2.3 Inclusion criteria

Participating subjects have to fulfil the following criteria:

| Inclusion Criteria                                                             |
|---------------------------------------------------------------------------------------|
| • out-patient status                                                                  |
| • male/female, age $\geq 60$ years                                                    |
| • depressive episode (moderate to severe according to ICD-10)                         |
| • Geriatric Depression Scale (GDS) $> 10$                                             |
| • Quick Inventory of Depressive Symptomatology (QIDS-C $> 10$ )                       |
| • MMST $> 25$ points                                                                  |
| • no or stable ( $\geq 6$ weeks) antidepressive pharmacological treatment at baseline |
| • no or stable antidepressive pharmacological treatment during 8-week intervention    |
| • sufficient German language skills                                                   |
| • written informed consent signed                                                     |

### 1.10.2.4 Exclusion criteria

Any of the following will exclude a subject from the trial:

| Exclusion criteria                                                                                      |
|----------------------------------------------------------------------------------------------------------------|
| • Bipolar depression                                                                                           |
| • Schizophrenia                                                                                                |
| • Other psychotic disorders                                                                                    |
| • Substance abuse or dependency                                                                                |
| • Dementia                                                                                                     |
| • Acute suicidality                                                                                            |
| • Anxiety disorder as stand-alone diagnosis (e.g. generalized anxiety disorder, panic disorder, social phobia) |

| Exclusion criteria                                                                                                                  |
|--------------------------------------------------------------------------------------------------------------------------------------------|
| • Obsessive-compulsive disorder as stand-alone diagnosis                                                                                   |
| • Participation in any another clinical trial parallel to this trial                                                                       |
| • Additional psychological/psychotherapeutic treatment throughout the treatment period                                                     |
| • Regular use with scheduled dosing of Benzodiazepines (not PRN)                                                                           |
| • Severe or instable medical condition, which clearly impacts on depression or on the ability to participate in the trial                  |
| • Brain disease with severe functional impairment that impacts the ability to participate in the trial (e.g. aphasia, Parkinson's disease) |

Any of the following will exclude a subject from the Magnetic Resonance Imaging (MRI) acquisition, if applicable:

| Exclusion criteria                                                                                                      |
|--------------------------------------------------------------------------------------------------------------------------------|
| • History of cardiac pacemaker, defibrillator or neurostimulator implantation                                                  |
| • Insulin or infusion pump                                                                                                     |
| • Cochlear, otologic or ear implant                                                                                            |
| • Any implant held in place by a magnet                                                                                        |
| • Tissue expanders (plastic surgery)                                                                                           |
| • Implanted catheter, clamp, clips, valves, or other metal                                                                     |
| • Tattoos or permanent makeup                                                                                                  |
| • History of metalworking                                                                                                      |
| • Injury with shrapnel or metal slivers                                                                                        |
| • Injury to the eye involving metallic object or fragment                                                                      |
| • Recent major surgery                                                                                                         |
| • History of major head trauma with loss of consciousness                                                                      |
| • Neurological disease (e.g. epilepsy, stroke, Parkinson's disease, multiple sclerosis)                                        |
| • Untreated or unstable cardiovascular, pulmonary, liver or kidney disease (e.g. unstable hypertension or cardiac arrhythmias) |
| • Claustrophobia                                                                                                               |
| • Weight > 160 kg                                                                                                              |

### 1.10.3 Removal of subjects from the trial

A subject may terminate participation in the trial at any time without providing a reason and without any personal disadvantage. Additionally, the Investigator can stop the participation of a subject after consideration of the benefit/risk ratio. Other possible reasons for the Investigator to discontinue a subject's trial treatment or participation include:

- Any relevant deterioration in the health of the subject possibly impacting the participation in the trial, including adverse events, severe medical condition, major surgery, laboratory parameters, vital signs or other safety parameters at the discretion of the Investigator.
- Regular use with scheduled dosing of Benzodiazepines (not PRN) or change of antidepressive pharmacological treatment during 8-week intervention.
- Parallel psychiatric or psychotherapeutic interventions (including but not limited to ECT, TMS, tDCS, VNS) during the treatment period.
- Technical grounds (e.g. subject moves away).

The Investigator must prepare a detailed written explanation for the LPI and the EC/IRB where applicable. The LPI and CTCC should be informed within three business days about the withdrawal of a subject from the trial.

In the single centre pilot study (data provided by [name]) [19], the attrition rate was 11% at the follow-up visit at six months after the end of the treatment. In this multicentre trial an attrition rate of 20% has been estimated, which seems realistic since the population is highly similar to that of the pilot study.

#### 1.10.3.1 Notification of discontinuations

The LPI and CTCC must be informed within three business days about any removal of a subject from the trial including the reason. The Investigator must prepare a detailed written explanation for the LPI.

#### 1.10.4 Trial completion

##### 1.10.4.1 Subject definition and subject completion

See Section 11.1.

##### 1.10.4.2 Procedures for handling of replacements, withdrawals or drop-outs

For all subjects who terminate the trial prematurely the Investigator must compile a precise written documentation including the reason for premature termination. Subjects who withdraw or stop treatment prematurely (drop-out, withdrawal) will not be replaced. The Investigator should make the attempt to monitor patients after drop-out and, if feasible, to conduct the follow-up outcome assessments.

##### 1.10.4.3 Premature termination of the trial

The trial will be stopped for the individual study participant, if the individual:

- Withdraws the informed consent.
- Develops a medical condition, which prevents participation in the trial.
- Experiences worsening of depression, which requires inpatient treatment or change of antidepressive medication.
- Develops acute suicidality.

The trial may be prematurely terminated by the respective competent local EC or the Lead Principal Investigator, if:

- The perception of the benefit/risk ratio becomes unfavourable for the continuation of the trial.
- The risk-benefit balance for the trial subject changes markedly.
- It is no longer ethical to continue treatment.
- It is no longer practicable to complete the trial.

However, our trial and study protocol are not to be expected to harm any subject but to improve outcomes. We do not expect that the trial has to be stopped in advance.

A decision to cease the trial is binding on all Investigators. Clinical Trials Centre Cologne, as well as the principal Investigators in each centre, must be informed immediately on the discontinuation of the trial. If the trial is prematurely terminated or suspended for any reason, the Investigator should promptly inform the subjects, should assure appropriate follow-up for the subjects, and inform the institution where the trial was being performed.

Participating centres, which fail to include the estimated number of subjects or to guarantee treatment in accordance to study protocol, will be closed.

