#### 1.11.3.4 Post-treatment phase

End-of-treatment primary and secondary outcomes (T2) will be gained in week 10 after completion of all 15 therapy sessions. The following outcomes will be obtained by the blinded rater at the end of treatment:

a) *Questionnaires:*

- Geriatric Depression Scale (GDS)
- Quick Inventory of Depressive Symptomatology Clinician-Rated Version (QIDS-C)
- Geriatric Anxiety Inventory (GAI)
- Patient-Reported Outcome in Major Depressive Disorder (PRO-MDD)
- WHO Quality of Life (WHOQOL-OLD and WHOQOL-BREF)
- Health Status (SF 36)
- Insomnia Severity Index (ISI)
- Epworth Sleepiness Scale (ESS)
- REM Sleep Behavior Disorder Screening Questionnaire (RBDSQ)

A qualitative interview will be performed at the end of the treatment period to assess individuals' needs and goals met and not met by the intervention.

If applicable to subject:

b) *Blood measurement:*

After completion of the treatment (T2) venous blood samples will be obtained from the subject for epigenetic analyses, measurement of Amyloid- $\beta$ , NFL, PBMCs, Metabolomics, Proteomics and miRNA analyses. The total volume of the blood draws will not exceed 50 ml.

c) *MRI:*

A Magnetic Resonance Imaging (MRI) acquisition of the subjects' brain will be performed at T2 to obtain a high-resolution structural image (T1 and T2 FLAIR) of the subjects' brain after the psychotherapeutic intervention. Furthermore, a resting-state fMRI will be acquired as well as Diffusion Tensor Imaging (DTI) of the subjects' brain at end-of-treatment (T2).

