### 2.6.3 Primary analysis

The primary objective of this study is to test the hypothesis that a 15-session individually delivered cognitive behavioural therapy (CBT) specific for late life depression (LLD) is of superior efficacy in reducing symptoms of depression in comparison with a supportive unspecific intervention (SUI) of the same quantity in subjects with LLD.

The primary outcome measure „change in GDS from baseline to end-of-treatment (week 10)“ is evaluated by a mixed model for repeated measures (MMRM) with fixed effects baseline, therapist, group, time and the interaction group\*time (ARH1-structured covariance matrix over time) with corresponding marginal means and contrast tests. Data from low recruiting therapists (i.e. < 4 subjects) are pooled by study centre. (In a supplementary analysis all therapists are pooled by centre.) The potential clustering of observations of participants by therapist or centre will be investigated by multilevel modelling. Since mixed models can be expected to yield valid results only in case of missingness-at-random, multiple imputation approaches are taken to assess the robustness of the results. Specifically, missing values due to death, illness or chance are separately imputed assuming mixtures of missingness-not-at-random patterns. Imputation data sets are post-processed by multiplication with factors and addition of offsets (tipping point analysis). Proxy measures are taken into account to ameliorate the effects of attrition.

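### Week-10 GDS is not clearly required after stops for worsening or acute suicidality, and the SAP gives such stops no missing-not-at-random class or offset range

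*Combined protocol and SAP*

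**What the plan says.** **Stopping.** Protocol 1.10.4.3: "The trial will be stopped for the individual study participant, if the individual" meets one of four conditions. Two of them concern the course of the depression: "Experiences worsening of depression, which requires inpatient treatment or change of antidepressive medication", and "Develops acute suicidality". Section 1.10.3 adds a discretionary list, introduced by "Other possible reasons for the Investigator to discontinue a subject's trial treatment or participation include". That list includes relevant deterioration in health and a change of antidepressant during the 8 weeks.

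**Data after stopping.** Protocol 1.10.4.2: "The Investigator should make the attempt to monitor patients after drop-out and, if feasible, to conduct the follow-up outcome assessments". Section 1.10.1 defines drop-out (stopping before session 9, or being otherwise lost before the final examination) separately from withdrawal (stopping, or being withdrawn by the investigator, for trial-related reasons such as an adverse event).

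**Timing of T2.** Protocol 1.11.3.4: "End-of-treatment primary and secondary outcomes (T2) will be gained in week 10 after completion of all 15 therapy sessions"; 1.11.3 says much the same. Section 1.11.3.6 and SAP 2.4.2 give week 10 with no condition on sessions.

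**Analysis.** SAP 2.6.3 uses an MMRM and acknowledges that it is valid only under missingness at random (MAR). For robustness, "missing values due to death, illness or chance are separately imputed assuming mixtures of missingness-not-at-random patterns", followed by a tipping point analysis with factors and offsets. The full analysis set (SAP 2.2.1) requires at least one valid outcome assessment after baseline.

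**The concern.** The triggers in 1.10.4.3 are themselves poor outcomes on the construct that the GDS measures. If they end observation as well as sessions, the missing week-10 values are missing for reasons tied to the primary endpoint. The MMRM would then predict those values from the participant's earlier scores and from participants who stayed. That prediction may be too favourable for someone who stopped because the illness worsened.

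Two things are at stake. The first is the week-10 contrast, if the arms lose different shares of such participants or lose participants of different severity. The second is the intention-to-treat claim, because a participant who stops before T1 and is not reassessed does not enter the primary analysis at all. A value that was not collected at week 10 cannot be recovered later, so the protocol wording matters more than the imputation model.

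**Working it through.** **Step 1. Is week-10 GDS required after such a stop?**

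| Section | What it settles | What it leaves open |
|---|---|---|
| 1.10.4.3 | Worsening as described, or acute suicidality, ends the trial for the individual | Whether assessments also end |
| 1.10.3 | Investigator may end treatment or participation | Which of the two applies, and when |
| 1.10.4.2 | Assessments are attempted after drop-out, if feasible | Whether withdrawals are included: the preceding sentence names both groups, this one only drop-out |
| 1.10.1 | Drop-out and withdrawal differ | Where a stop for worsening belongs |
| 1.12.2.1 | Worsening and suicidal thoughts or plans are adverse events | Whether each is trial-related (judged case by case under 1.12.2.4 and 1.12.2.7) |
| 1.11.3, 1.11.3.4 | T2 follows all 15 sessions | When T2 falls for someone who stops early |
| 1.11.3.6, SAP 2.4.2 | T2 is at week 10 | – |

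No section requires week-10 GDS after a 1.10.4.3 stop, and none forbids it. The sections have to be reconciled.

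**Step 2. The plan's own figures.** Inputs (protocol 1.14.1, SAP 2.1.7): difference 2.5, d = 0.4, so SD = 2.5/0.4 = 6.25; 80% power; two-sided 5%. This gives 99 per group, and 99/0.8 = 123.75, so 124 per group and 248 in total. The plan's numbers reproduce and this point does not change them. The planned standard error is 6.25 × √(2/99) = 0.89.

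**Step 3. Size of the possible bias.** Let m be the share of an arm whose week-10 value is lost through such stops, and δ the amount by which the true GDS exceeds the MAR prediction. Then

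true benefit − MAR estimate = δ_SUI × m_SUI − δ_CBT × m_CBT,

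which with a common δ is δ × (m_SUI − m_CBT). The documents give neither δ nor m, so all values below are assumptions.

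| δ (points) | Arm difference in m | Shift | Share of 2.5 |
|---|---|---|---|
| 4 | 3 percentage points | 4 × 0.03 = 0.12 | 5% |
| 6 | 5 percentage points | 6 × 0.05 = 0.30 | 12% |
| 8 | 10 percentage points | 8 × 0.10 = 0.80 | 32% |

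- Equal m and equal δ: shift 0.
- Equal m of 10% but δ of 8 (SUI) and 4 (CBT): 0.80 − 0.40 = 0.40.
- More stops under SUI: MAR understates the benefit of CBT. More stops under CBT: MAR overstates it.

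**Step 4. What the middle case does to the test** (normal approximation, 99 per group).

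- A true 2.5 estimated as 2.2: power is Φ(2.2/0.888 − 1.96) = 70%, against 80% at 2.5.
- No true difference, with 0.30 of bias towards CBT: the chance of falsely concluding that CBT is superior is Φ(0.30/0.888 − 1.96) = 5.2%, against 2.5%.

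**Step 5. Simulation check.** Three GDS time points, true difference 2.5, 500 per arm, week-10 values predicted from baseline, T1 and arm. With loss partly or wholly determined by the change to week 10, equal 10% loss returned about 2.5. Loss of 5% (CBT) and 15% (SUI) returned 1.8 to 2.0; the reverse returned 3.0 to 3.2. When loss was unrelated to outcome, all three patterns returned about 2.5.

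**The case against.** A reader might infer that the plan discards the worst week-10 scores and then treats them as missing at random. The documents do not support that.

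- **Loss is possible, not prescribed.** Section 1.10.4.2 does ask for assessments after drop-out. The reasons for drop-out in 1.10.1 are examples, and worsening from the underlying illness need not be trial-related, so some of these participants are covered.
- **Medication change alone does not end the trial under 1.10.4.3**, which requires worsening. By itself it is only a discretionary reason in 1.10.3.
- **T2 is not firmly tied to 15 sessions.** Section 1.11.3.6 and SAP 2.4.2 fix it at week 10. A per-protocol set with a 9-session minimum inside the full analysis set, and the planned complier analysis, both presuppose outcomes from people with incomplete treatment.
- **MAR applies to the primary model only.** Illness could be read to include depressive worsening, and an offset tests worse-than-predicted values whatever their cause. After T1, the MMRM also uses the T1 score.
- **The analysis is not restricted to people who did not deteriorate.** Deterioration that triggers no stop remains observed.
- **The inclusion criterion "no or stable antidepressive pharmacological treatment during 8-week intervention" can only be judged after randomisation**, but 1.11.4.3 states the same rule as an on-study restriction. Moving it would change no result.
- **The contrast may be little affected.** Both arms receive the same quantity of treatment from the same therapists. The 0.30-point case is about a third of a standard error, and a 10-point imbalance in such stops alone would be extreme beside the pilot's 11% total attrition. Inpatient care or a medication change might also improve GDS by week 10, so δ need not be positive.

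All of this limits the size and certainty of the problem. What remains is that collection after these stops is unclear and qualified by feasibility, that no class is named for them, and that no offset range is set. Proxy measures do not close the gap: the schedule lists no proxy instrument, and the GDS is a self-rating.

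**Conclusion.** The point holds as a gap between sections rather than as a demonstrated bias. As written, week-10 GDS after outcome-related stops is not required and may be lost. The primary MMRM then relies on MAR for those values, and stops before T1 without reassessment leave the full analysis set. The planned sensitivity analyses are of the right kind but are not specified for this mechanism.

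Bias in the contrast needs a difference between arms in exit rate or severity. Its direction is unknown. Its size, 0.12 to 0.80 GDS points with a middle case of 0.30 (12% of 2.5), rests entirely on assumed values of δ and m. The sample size is unaffected. This should be fixed: the remedy is cheap, and uncollected values are lost for good.

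**What to change.** Leave every clinical stopping criterion as it stands.

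1. **Protocol.** Reconcile 1.10.1, 1.10.3, 1.10.4.2, 1.10.4.3, 1.11.3 and 1.11.3.4 so that stopping treatment does not end observation. State that GDS at T1, T2 and T3 is sought from every randomised participant after any drop-out or withdrawal, unless consent to data collection is withdrawn. Place T2 at week 10 whatever the number of sessions completed, as 1.11.3.6 and SAP 2.4.2 already imply.
2. **SAP 2.6.3, primary model.** State that these values enter the primary MMRM. They will reflect any care given after the stop, which is consistent with the intention-to-treat principle the plan adopts.
3. **SAP 2.6.3, sensitivity.** Name stops for worsening, medication change, hospitalisation or suicidality as a separate missing-not-at-random class, with a pre-specified offset range that may differ by arm (for example 0 to 10 GDS points, varied independently in each arm). Report the number of such stops by arm and by whether they occurred before T1.

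The cost is wording plus some extra contacts with participants who are unwell, which 1.10.4.2 already partly foresees. Some values will still be missing, which is why the third change is needed alongside the first.
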